## Abstract

**Background:**

Although the gut microbiome plays a crucial role for maintaining overall host homeostasis and metabolism, it is significantly influenced by dietary changes, leading to substantial temporal variations in microbial composition within and between individuals. Despite this, incidental fecal sampling remains the standard method for microbiome assessment. Recently, the blood microbiome, defined by microbial DNA (cmDNA) circulating in the bloodstream, has emerged as a potentially more stable and integrated alternative. Preliminary data suggest that blood microbiome analysis may offer more consistent insights than fecal-based approaches, although the methodological validity of the approach has been questioned.

**Method/design:**

This study aims to establish or rule-out cmDNA as a representative of the gut microbiome. In a prospective, single-arm crossover trial, effects of dairy product withdrawal and reintroduction of a yoghurt with a known consortium of bacteria will be assessed in healthy volunteers aged 18–65. Participants will first abstain from all dairy products, a phase expected to reduce yogurt-associated cmDNA in the bloodstream. Yogurt will then be reintroduced, during which reappearance of cmDNA of specific bacteria (especially LGG, LA-5 and BB-12) is anticipated. Shotgun metagenomic sequencing will be used to track cmDNA dynamics over time. This longitudinal sampling approach will provide experimental evidence supporting the existence and responsiveness of the circulating microbiome, while also revalidating the bioinformatic pipeline used for its analysis.

**Conclusion:**

This pilot study will test whether blood-derived microbial DNA can serve as a valid surrogate for gut microbiome composition. If successful, this approach may provide a more stable and integrative alternative to fecal sampling and support future biomarker development and mechanistic research.

**Clinical trial registration:**

NCT06944002.

## Introduction

1

Ecological DNA (eDNA) is a concept that enables comprehensive descriptions of all organisms present within an ecosystem. The gut microbiomes can be viewed as a specific application of this concept, representing the diverse community of microorganisms inhabiting the gastrointestinal tract [1,2]. In principle, a full description of the gut microbiome should theoretically include all microbial domains, bacteria, viruses, archaea, fungi, as well as other organisms such as worms and phages. However, accurately profiling the gut microbiome remains challenging due to inherent temporal variability and technical limitations. For example, the widely used 16S rRNA gene sequencing method primarily targets bacteria and overlooks other important taxa [3]. Despite these challenges, detailed and accurate characterization is critical, given the gut microbiome's pivotal role in maintaining host health and homeostasis [4,5].

To address the challenges of sampling the intestinal microbiome, most researchers currently rely on fecal analysis. While convenient, this approach has notable limitations. Our team has pioneered advanced technical methodologies, including a double-balloon endoscopic study in healthy volunteers, to comprehensively characterize the gut microbiome in situ [6]. However, fecal samples often fail to accurately reflect the mucosa-associated (adherent) microbiota, which resides in close proximity to epithelial cells and may exert more direct effects on host physiology than luminal bacteria [7,8]. Moreover, fecal microbiomes exhibit considerable heterogeneity, with microbial composition varying across different portions of a single sample. Additional technical barriers include the inefficiency of standard DNA extraction protocols in recovering eukaryotic organisms. Compounding these issues is the strong influence of diet on fecal microbial profiles, distinct microbial communities can emerge following different meals, such as breakfast versus dinner [9]. Collectively, these limitations underscore the need for alternative, more stable and representative sampling strategies capable of generating microbiome data predictive of host health.

An emerging strategy for microbiome analysis involves profiling the blood microbiome, a novel approach that captures microbial signals from multiple body compartments, particularly the gut [10]. The blood microbiome comprises circulating microbial DNA (cmDNA), which consists of fragmented genetic material from microorganisms rather than intact, viable cells. The precise mechanisms through which microbial DNA enters the bloodstream remain unclear [11], though the gastrointestinal tract is considered a major source, especially in the context of impaired gut barrier integrity, a feature commonly observed in chronic diseases. Blood-derived microbiome signatures have demonstrated potential as non-invasive biomarkers for a range of conditions, including diabetes, cardiovascular disease, and cancer, with preliminary evidence suggesting they may even distinguish among different cancer types [10,12]. Despite this promise, the field is subject to ongoing debate, largely due to technical limitations in bioinformatic analysis and the risk of contamination or other artifacts [13,14], underscoring the need for rigorous proof-of-concept studies. These challenges highlight the urgent need for rigorous, well-controlled proof-of-concept studies, a gap that our current research aims to address.

Building on previous findings, we observed that *Lactococcus lactis*, a dairy-dependent intestinal bacterium, is undetectable in human stool within four days of dairy withdrawal, but reappears rapidly upon dairy reintroduction [15,16]. Although the precise half-life of bacterial DNA in human blood is unknown, studies on cancer- and fetal-derived cell-free DNA suggest it is typically less than 24 h [17]. Based on this, a 10-day period of dairy exclusion should markedly reduce cmDNA from milk-associated microbes, with subsequent reemergence following dairy intake.

In this study, we describe the rationale, bacterial-species controlled, and analytical framework for a single-arm crossover trial evaluating the effects of yogurt consumption on the blood microbiome in healthy volunteers. The primary aims are: (1) to assess the presence and abundance of yogurt-dependent intestinal bacterial (YDB) DNA in both blood and fecal samples, and (2) to characterize broader microbiome DNA signatures, including bacteria, viruses, and archaea, in these biological compartments. We hypothesize that yogurt consumption, known to beneficially influence the fecal microbiome and immune function, will induce detectable alterations in cmDNA profiles, reflecting a convergent microbiome signature between the gut and bloodstream. Successfully capturing this phenomenon in a controlled dietary intervention would provide critical proof-of-concept for the presence and dynamic nature of the human blood microbiome.

## Methods

2

### Study design

2.1

We will perform a within-subjects crossover trial with a single arm to study the effect of yogurt on the blood and fecal YDB levels in healthy volunteers. Participants will first undergo a 10-day period of dairy product withdrawal. Given that the half-life of bacterial DNA in blood is likely less than 24 h, a 10-day withdrawal period should be sufficient to substantially reduce circulating DNA fragments originating from *L. lactis*. Following the reintroduction of dairy (via yogurt consumption that is host to LGG, LA-5 and BB-12 cultures), we expect these specific bacteria and other YDB DNA to reappear in the bloodstream. While the precise kinetics of this reappearance are not yet known, our study is designed to detect these temporal changes and establish a foundation for understanding the dynamic relationship between dietary intake, the gut microbiome, and the blood microbiome.

This study is approved by the ethics committee of Erasmus Medical University Center Rotterdam in May 2025 (NL88008.078.24) and is registered at www.clinicaltrials.gov (NCT06944002), hence prior to participant's enrollment. This study will be conducted in accordance with the principles of the Declaration of Helsinki (75th WMA General Assembly, Helsinki, Finland, October 2024) and the Medical Research Involving Human Subjects Act (WMO). Interested volunteers will be provided with detailed information about the study and will give written informed consent prior to participation.

Participants will be studied at multiple time points using a within-subject crossover design (Fig. 1). At baseline, prior to any dietary intervention, blood and stool samples will be collected. Following this, participants will abstain from all dairy products for 10 days, after which a second set of blood and stool samples will be collected to confirm the expected disappearance of YDB DNA from both fecal and circulating microbial DNA pools.

**Fig. 1 fig1:**
[figure not shown]
Study design. In this within-person crossover trial, the volunteers will be studied multiple times: a baseline sample of blood and stool will be collected before the withdrawal of any dairy product. Ten days later, the same samples will be collected again to verify if milk and/or yogurt-associated bacteria disappear from the stool and the blood DNA. Subsequently, volunteers will be instructed to drink minimal 700 mL yogurt during breakfast for 7 consecutive days. Three time points will be chosen to capture the dynamics of yogurt-associated DNA gut-to-blood translocation: 24 h, 48 h, and one week after the reintroduction of dairy products. Participants will be invited to visit the hospital for a total of five times. The dairy products used in this study will be provided by the investigational team.

Subsequently, participants will reintroduce dairy into their diet by consuming 700 mL of yogurt daily for seven consecutive days, an amount consistent with recommendations from the United States Dietary Guidelines [18]. Given the current lack of data on the kinetics of bacterial DNA translocation from the gut to the bloodstream, we will collect post-intervention blood and stool samples at three distinct time points: 24 h, 48 h, and one week following the reintroduction of dairy. During this reintroduction phase, participants will also be permitted to consume other dairy products in addition to yogurt.

### Participant recruitment

2.2

Healthy volunteers who are interested in participating in the study will be invited. To do this, flyers with contact information (for the secretary) will be posted within the university. All participants expressing interest will receive a study description document that they can read and evaluate at home. Participants will be given one week to make their decision. If they have additional questions, they may consult the leading investigator. One week later, participants will be approached again. After providing sufficient information and answering any questions, participants who agree to participate will be requested by the authorized person to sign the informed consent form and to send it to the coordinating investigator or bring the form to the hospital to sign in the presence of the coordinating investigator. The process of the study is shown in Fig. 2.

**Fig. 2 fig2:**
[figure not shown]
Study schema. This study requires to include data from at least 10 participants.

### Inclusion criteria

2.3

1)Age 18–65 years2)18.5 =< BMI <25 kg/m23)All genders included4)Not be lactose intolerant5)Willing to consume milk

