### **Exclusion criteria** (self-report)

**2.4**

1)Regular use medications such as antibiotics, steroids, beta blockers, and adrenergic-stimulating agents2)Regular use prebiotic and/or probiotics apart from yogurt and young soft cheese3)Antibiotic intake in the previous months4)Daily consumption of more than 10 cigarettes, a minimum quantity known to significantly affect the gut microbiome [19].5)Chronic diseases including type 2 diabetes, hypertension, fatty liver disease, cancer, or autoimmune disease6)Internal diseases, including those of the gastrointestinal tract, lung, heart, vasculature, liver, and kidney7)Eating disorder or unconventional eating habits8)Participation in another study9)Women: pregnancy and breastfeeding

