#### Primary objective

2.5.1

The primary objective is to examine yogurt-dependent bacterial (YDB) DNA counts in fecal and blood samples before and after dairy consumption. YDB, such as *Lactococcus lactis*, are transient residents of the human gut, only present following dairy intake, and therefore represent modifiable components of the intestinal microbiome. Detection of YDB DNA fragments in the bloodstream after dairy reintroduction will provide definitive evidence on the extent to which the blood microbiome reflects relevant changes in the intestinal microbiome. In this specific study, the use of a commercial yoghurt (but verified by independent agar growth testing) containing a defined consortium of bacteria adds signature species whose detection provides convincing signals in this respect.

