#### Baseline visit for milk withdrawal

2.7.2

Two weeks after the screening, participants will attend a morning baseline visit at the hospital. During this visit, medical history, body composition (weight, waist circumference, and BMI), and blood pressure will be assessed. Blood samples will be collected for blood microbiome analysis, and participants will be asked to provide a fecal sample (Table 2).From this day onward, participants will eliminate all dairy products from their diet for 10 consecutive days. Compliance with diary product withdrawal will be confirmed by direct interrogation at the sampling times, a questionnaire and by detecting YDB in the fecal samples using shotgun sequencing. Participants apparently not dairy-product withdrawn will be excluded from the final analysis and replaced by newly-recruited subjects.

**Table 1 tbl1:** Overview of study procedures.

	Study period (Days)					
	Enrollment	Milk withdrawal	Intervention			
Time	T = −15∗ day	T = −10 day	D_0_	D_1_	D_2_	D_7_
Suitability screening	X					
Informed consent	X					
Intervention: Milk withdraw → Yogurt reintroduction						
Measurements						
Anthropometric variables	X	X	X	X	X	X
Blood microbiome assessment		X	X	X	X	X
Fecal microbiome assessment		X	X	X	X	X
BMI		X	X	X	X	X
Blood pressure		X	X	X	X	X
Routine laboratory measurements		X	X	X	X	X

Note: D, Days; BMI, body mass index; ∗ will be differed depending on participant's availability.

**Table 2 tbl2:** Primary, secondary and exploratory outcomes.

Outcomes	Brief description	Time frame
Primary		
Blood MDB	Shotgun sequencing of whole blood DNA	−10, 0, 2, 3 and 7 days
Secondary		
Other blood microbes	Shotgun sequencing of whole blood DNA	−10, 0, 2, 3 and 7 days
The gut microbiome	Shotgun sequencing of fecal DNA	−10, 0, 2, 3 and 7 days
Exploratory		
BMI	Weight in kilograms and height in meters will be combined to report BMI in kg/m^2.	−10, 0, 2, 3 and 7 days
Blood pressure	Systolic and diastolic blood pressure will be assessed with a blood pressure monitor.	−10, 0, 2, 3 and 7 days

Note: MDB, milk-dependent intestinal bacteria.

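### The entry criteria require no recent dairy or yogurt intake, so some participants may have no yogurt-dependent bacterial DNA to lose during the withdrawal phase

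*Protocol article*

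**What the plan says.** Section 2.3 lists five inclusion criteria. Two concern dairy: "Not be lactose intolerant" and "Willing to consume milk". The first is about tolerance and the second about willingness.

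Section 2.4 excludes "Regular use prebiotic and/or probiotics apart from yogurt and young soft cheese", so yogurt is allowed but not required. It also excludes "Eating disorder or unconventional eating habits", without defining the term. The screening assessment in section 2.7.1 covers diseases, medication and smoking, and mentions no dietary intake.

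The abstract gives the purpose of the first phase: "Participants will first abstain from all dairy products, a phase expected to reduce yogurt-associated cmDNA in the bloodstream". Section 2.1 says the second set of samples is taken "to confirm the expected disappearance of YDB DNA from both fecal and circulating microbial DNA pools". The T-10 sample precedes any dietary intervention, so no dairy run-in comes before it.

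Under section 2.7.2, adherence to withdrawal is checked by interview, by questionnaire and "by detecting YDB in the fecal samples using shotgun sequencing". Participants who appear not to have withdrawn are excluded and replaced. Section 2.9 makes the change in blood YDB relative abundance over all five time points the primary outcome, analysed by repeated measures ANOVA.

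**The concern.** A test of disappearance needs something present at the start. Section 2.5.1 describes YDB as "only present following dairy intake, and therefore represent modifiable components of the intestinal microbiome", and the Introduction reports that one such species can no longer be detected in stool within four days of stopping dairy. A volunteer who tolerates lactose and would drink milk, but has had no dairy in the days before T-10, meets every listed criterion and is expected to be negative at both T-10 and D0. For that person the withdrawal phase is empty and T-10 duplicates D0.

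This matters because the trial has one arm and no parallel control. Its within-subject defence against contamination and database misclassification is the longitudinal pattern: a fall on withdrawal, then a rise on reintroduction. A participant who cannot fall contributes only a before-after comparison. In a study of 10, a few such participants would noticeably weaken the evidence for the fall.

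**Working it through.** **Step 1: can a non-consumer enter and remain?** The sections, taken in order:

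- Section 2.3: lactose tolerance and willingness, no intake. Eligible.
- Section 2.4: yogurt permitted, not required. Not excluded, unless total dairy avoidance is judged an unconventional eating habit.
- Section 2.5.1: no dairy intake means no YDB. Expected negative at T-10.
- Section 2.7.2: compliance is shown by absence of dairy and of fecal YDB at D0. Passed trivially.
- Section 2.7.2: replacement applies to those who did not withdraw. Not replaced.
- Section 2.8.4: stool is taken at every time point and goes through the same pipeline as blood. Negative status at T-10 is visible after the fact, but no stated rule uses it.

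**Step 2: how many?** The documents give n = 10 (section 2.6), chosen by precedent without an effect size, SD or power, so there is no planned figure to reproduce. The share q of eligible volunteers without YDB at T-10 is not given; it is assumed to lie between 0.1 and 0.5.

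Expected number = 10q. P(at least 3) = 1 − Σ(k = 0 to 2) C(10,k) q^k (1−q)^(10−k).

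| q | Expected of 10 | P(at least 1) | P(at least 3) |
|---|---|---|---|
| 0.1 | 1 | 0.651 | 0.070 |
| 0.2 | 2 | 0.893 | 0.322 |
| 0.3 | 3 | 0.972 | 0.617 |
| 0.4 | 4 | 0.994 | 0.833 |
| 0.5 | 5 | 0.999 | 0.945 |

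For example, at q = 0.5: 1 − (1 + 10 + 45)/1024 = 0.945.

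**Step 3: effect on the T-10 to D0 contrast alone.** As an illustration, assume a mean drop of 1.0 SD in carriers and none in non-carriers, with SD 1 for the change in both, n = 10, and a paired t-test at two-sided 0.05 (100,000 simulated trials). Power is 0.81 at q = 0, 0.68 at 0.1, 0.55 at 0.2, 0.44 at 0.3 and 0.25 at 0.5. The protocol does not plan this test; the figures only show how sensitive the contrast is.

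**Step 4: effect on the planned five-time-point analysis.** As an illustration, put the YDB level at 1 with dairy and 0 without. The mean profile over T-10, D0, D1, D2 and D7 is (1−q, 0, 1, 1, 1). The between-time sum of squares is:

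- q = 0: mean 0.80; 4 × 0.20² + 0.80² = 0.80.
- q = 0.25: mean 0.75; 0 + 0.75² + 3 × 0.25² = 0.75.
- q = 0.5: mean 0.70; 0.20² + 0.70² + 3 × 0.30² = 0.80.

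The mean signal hardly moves, because the rise after D0 supplies most of it. A mixture at T-10 does add between-person variance of q(1−q) there (0.09 at q = 0.1, 0.25 at q = 0.5), which feeds into the subject-by-time error.

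**The case against.** The strongest reply is that the decisive test is reappearance. Section 2.5.1 rests the proof on finding YDB DNA in blood after reintroduction, and section 2.6 ties the choice of 10 volunteers to trends over the seven intervention days. A non-consumer has a clean D0 and is fully informative for that test. This stands, and it limits the point to the withdrawal step.

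A reader might also infer that these participants would go unnoticed and that a flat blood profile would be taken as failure of the method. The documents do not support that. Stool from T-10 is sequenced, and flat stool with flat blood is concordance. What remains is that no stated rule uses the result, and that by then a place among 10 has been spent.

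A reader might take the drop in power in Step 3 as a loss for the primary analysis. It is not: Step 4 shows that the mean signal of the planned ANOVA is almost unchanged.

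Nor do the documents establish that people who consume only dairy without live cultures would lack YDB DNA. The assay detects DNA fragments, and the withdrawal rationale refers to milk-associated microbes generally. The point is therefore confined to people without recent dairy or yogurt intake.

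Finally, the share of such people is unknown, and the exclusion of "Eating disorder or unconventional eating habits" may remove some of them. At a share of 10% the chance of three or more is only 7%.

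**Conclusion.** The point holds in limited form. The listed criteria admit people who, on the protocol's own account of YDB, have nothing to lose between T-10 and D0, and neither the compliance check nor the replacement rule deals with them. The damage is to the T-10 to D0 contrast and to the error term of the five-time-point analysis. The reappearance contrast is intact, so the primary objective is weakened and not lost.

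If 10% to 50% of volunteers are non-consumers, 1 to 5 of 10 participants are expected to be uninformative for disappearance, with a probability of 7% to 95% that three or more are. These figures rest on an assumed share and on independent recruitment of participants; the documents supply no estimate.

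**What to change.** Reword inclusion criterion 5 to require regular intake of yogurt or other fermented dairy before the T-10 visit, plus willingness to stop and restart. Check it at screening and at T-10, using the interview and questionnaire already planned for withdrawal compliance. Select on reported intake and not on measured YDB, so that selection on the outcome does not produce an artificial fall through regression to the mean. In addition, state that each participant's T-10 to D0 blood change will be interpreted alongside their T-10 stool YDB status.

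The cost is one criterion, one question on intake and a slightly narrower pool for a 10-person study. The change does not guarantee that LGG, LA-5 or BB-12 are present at baseline, since a habitual yogurt eater need not carry those particular bacteria; the stool-based reading is needed for that reason too.

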### **Exclusion criteria** (self-report)

**2.4**

1)Regular use medications such as antibiotics, steroids, beta blockers, and adrenergic-stimulating agents2)Regular use prebiotic and/or probiotics apart from yogurt and young soft cheese3)Antibiotic intake in the previous months4)Daily consumption of more than 10 cigarettes, a minimum quantity known to significantly affect the gut microbiome [19].5)Chronic diseases including type 2 diabetes, hypertension, fatty liver disease, cancer, or autoimmune disease6)Internal diseases, including those of the gastrointestinal tract, lung, heart, vasculature, liver, and kidney7)Eating disorder or unconventional eating habits8)Participation in another study9)Women: pregnancy and breastfeeding

